#### Module 2 (survey).

For the standardized survey, a random sample of insured persons of two participating health insurance funds (Pronova BKK and mkk – meine Krankenkasse) are contacted who are aged 18 years or older and for whom the diagnosis U09.9! was documented in the quarter available at the time of the survey with a complete database and at least one other quarter in the previous three quarters (M2Q criterion) [30]. Exclusion criteria are: deceased, not continuously insured during the above-mentioned period, has refused contact by SHI or the use of data for research purposes, lives abroad, has a protection mark (e.g., employee).

#### Module 3 (interviews).

No specific inclusion and exclusion criteria are defined in addition to the presence of a PCS diagnosis and age of 18 years or older. When selecting the interview partners, it is intended that the sample contains different genders, age groups, degrees of severity with regard to the existing PCS symptoms and different durations of PCS.

#### Module 4 (medical visits and assessments).

Patients are selected who meet the criteria for a PCS, were previously healthy, are housebound as a result of the disease (Bell 0–20) and are therefore unable to attend the outpatient clinic, are living in Berlin and wish to participate in the study.

### Data collection

#### Module 1 (routine data).

For the routine data analysis, a complete survey of the insured persons with the corresponding ICD diagnoses at the participating SHI is sought. We use socio-demographic data (§ 288 Social Code Book V) and claims data for healthcare, rehabilitation and nursing services (Social Code Book V and XI) (Table 1).

**Table 1 pone.0353270.t001:** Variables of the routine data collection.

Module 1a	Module 1b
• Basic demographic data (year of birth, sex, municipality key, employment status, care level) • Periods of incapacity to work, diagnosis • Outpatient treatment (diagnoses) • Outpatient hospital treatment (diagnoses) • Inpatient hospital treatment (diagnoses)	• Basic demographic data (year of birth, sex, municipality key, employment status, care level) • Periods of incapacity to work, diagnosis • Long-term care claims data • Outpatient treatment, diagnoses and costs • Medication • Outpatient hospital treatment, diagnoses and cost • Inpatient hospital treatment, diagnoses and costs • Rehabilitation (diagnosis, department, start and end of rehabilitation, assessment of work ability) • Therapeutic and assistive aids • Billing data for digital health applications

#### Module 2 (survey).

The hybrid survey is conducted both analogously (questionnaire sent back by post) and, alternatively, online.

The questionnaire surveys sociodemographic factors (e.g., age, gender, family status, migration history, place of residence) and socio-economic factors (educational and vocational qualifications, occupational status, household income). In addition, standardized scales are used, e.g., to measure subjective working capacity and health status, quality of life (QoL), cognitive status, level of activity, pre-existing conditions and accompanying symptoms (Table 2). Some project-specific questions, for example on treatment and satisfaction with healthcare, complement the standardized tools.

**Table 2 pone.0353270.t002:** Standardized instruments for the assessment of PCS patients.

Outcome	Instrument
General life satisfaction	Short scale for assessing general life satisfaction (L-1) [31]
Subjective work ability	Work Ability Score (WAS) [32]
Health-related quality of life	Short Form 12 Health Survey (SF-12) [33,34]
Functional capacity	Functional Capacity Questionnaire (FUNCAP27) [35]
Health problems	Self-Administered Comorbidity Questionnaire (SCQ_D) [36]
Psychological well-being	Patient Health Questionnaire (PHQ-4) [37]
Post-COVID-related complaints	Post-Covid Syndrome Score (PCS Score) [38]
ME/CFS diagnosis	SEID criteria [39]
Fatigue	Chalder Fatigue Scale [40]

#### Module 3 (interviews).

The semi-structured interviews are conducted by a researcher via video call or by phone (duration approximately 60 minutes). The semi-structured interview guide is based on the following categories: description of the illness and effects on everyday life (professional, social), perception of healthcare, barriers to using the healthcare system, acceptance and stigmatization, coping with the illness and expectations. The interviews are audio-recorded and transcribed according to Dresing and Pehl [41].

#### Module 4 (medical visits and assessments).

For severely affected patients, a diagnostic workup and an assessment of the nature and severity of the illness are to be conducted via home visits by a physician experienced in PCS and ME/CFS. In preparation for this appointment, patients will complete various digital questionnaires (structured medical history, Bell Scale, FUNCAP55, SF-36, MBSQ/Canadian Consensus Criteria, PHQ-4 Depression, EQ-5D-3L Quality of Life, COMPASS-31, Chalder Fatigue Questionnaire, ESS-Sleep). Patients may receive assistance from relatives with completing the questionnaires and with the organizational preparation of the appointment. Furthermore, the study physician will contact the patient's primary care physician (PCP) and review all prior medical reports.

The clinical evaluation during the home visit includes a comprehensive medical history and a physical examination, which essentially corresponds to the procedure of the ME/CFS diagnostic consultation. The examinations, which include handgrip strength measurement, may be reduced or omitted depending on the patient's level of tolerance, in order to avoid post-exertional malaise (PEM) wherever possible.

Following the appointment, a report will be generated and an individualized treatment plan developed for implementation by the PCP. Over a period of 6 months, the PCP, as well as the patients and their relatives, will receive professional support from the study team for the implementation of this plan. During the same period, the patient's condition will be monitored monthly using the FUNCAP55 questionnaire. At the end of the observation period, a one-time, more comprehensive digital assessment will be performed (Bell Scale, FUNCAP55, SF-36, MBSQ/Canadian Consensus Criteria, PHQ‑4 Depression/Anxiety, EQ-5D-3L Quality of Life, COMPASS-31, Chalder Fatigue Questionnaire, ESS-Sleep).

### Expert panel

The project is supported by an advisory board consisting of members of a patient association and representatives from outpatient care and rehabilitation facilities. This board forms the expert panel responsible for translating the findings of the analyses into practical recommendations for improving patient healthcare.

### Data management

Routine data analyses (Module 1) and analyses of survey data (Module 2) will be conducted using anonymised data. Re-identification of insured individuals will not be possible. Access to all datasets (Modules 1–4) will be restricted to members of the research team only.

### Sample size

#### Module 1 (routine data).

Since the planned routine data analysis involves a complete collection of the data of all insured persons of the participating statutory health insurances companies (SHI), no priori calculation of the sample size is carried out here. It is expected that data of around 13,500 PCS patients of 44 SHIs will be included.

#### Module 2 (survey).

A total of 2,854 people is contacted by post through two SHIs (Pronova BKK and mkk – meine Krankenkasse). Target response size is at least 200 affected individuals. This sample size allows for the determination of frequencies with a 95% confidence interval of approximately 4–7 percentage points (depending on the prevalence) around the point estimate. A conservative response rate of at least 7.5% is anticipated to ensure that, even after excluding invalid data and individuals who do not meet the inclusion criteria, at least 200 individuals can still be included in the analyses. A higher response rate is expected.

#### Module 3 (interviews).

A total of approximately 15 guided, problem-centred interviews is conducted with PCS patients in order to gain a detailed understanding of individual care trajectories and subjectively perceived barriers to care. The planned sample size is based on qualitative saturation principles, the expected information power of a purposively selected sample with heterogeneous symptom experiences but a focused research aim, and previous experiences from qualitative research involving post-COVID patients [42,43]. Data collection and analysis will be conducted iteratively, and thematic saturation will be monitored continuously. If relevant new themes continue to emerge, additional interviews may be considered.

#### Module 4 (medical visits and assessments).

A total of 15 PCS patients in the area of Berlin will be medically consulted and examined in their homes. The planned sample size was chosen to capture a relevant spectrum of severe healthcare situations and functional impairments among homebound PCS patients while allowing for in-depth physician-led assessments. Given the exploratory character of this Module, the substantial time and personnel requirements associated with home visits, and the limited physical capacity of severely affected patients, a sample size of approximately 15 participants was considered feasible and appropriate.

### Data analysis

#### Module 1 (routine data).

First, descriptive statistics will be conducted to describe the sample in terms of sociodemographics and comorbidities. In addition, subgroup analyses are planned. These will include group comparisons regarding symptom severity, disease progression and consequences (e.g., incapacity for work). The groups will be stratified by gender, age group, region (urban versus rural) and among other factors. The focus of all analyses is the PCS diagnosis in combination with other diagnoses, healthcare measures received, and periods of incapacity for work. The relationship between specific constellations of care pathways and symptom severity will be investigated using bivariate and multivariate methods. Binary logistic regressions (dichotomous dependent variable: incapacity for work yes/no) will be used to calculate the strength of various factors influencing the outcome. Further, a cost calculation of care pathways and identification of particularly cost-intensive care units will be carried out.

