It is also important to focus analyses on patients with particularly long periods of work disability and/or who are classified as eligible for a defined level of care. It can be assumed that they continue to require adapted care pathways but they have been the subject of hardly any current studies. It is also important to comprehensively examine old and very old PCS patients, their state of health and care trajectories, as well as their prognoses for being classified as needing long-term care.

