**Further research questions:**

What are the characteristics of persons affected by PCS (main diagnoses; previous illnesses/comorbidities; symptoms/disease burden; socio-demographic characteristics)?Where is the PCS diagnosis most frequently recorded (e.g., in primary care practices)?Which particular features characterize old and very old PCS patients?Which conditions lead to particularly long-term work disability and/or need for care in PCS patients?What regional differences in the healthcare of PCS patients can be identified?What personal view do PCS patients have on their healthcare?What is the long-term care situation of PCS patients, and can care deficits be identified?What improvement measures/potential for PCS patients can be identified from the collected data?

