#### Module 1 (routine data).

The system of company health insurance funds (“BKK”) is a large association of statutory health insurance companies (SHI) in Germany. The 44 participating SHIs represent 7.8 million insured persons and are all members of the BKK Federal Association (BKK Dachverband e.V.). The socio-demographic data of BKK insured persons show that they do not differ significantly in their characteristics or structure from the respective reference population of all SHI insured persons in Germany. In the BKK insured population, the genders are almost equally represented. The average age is 43.0 years. Half of the BKK insured individuals (49,6%) are employed; 22.7% are family members; 19.8% are retired. In terms of age, gender, and occupational characteristics, employed BKK members do not differ significantly from all employees subject to social insurance contributions in Germany. The only exception is that a higher proportion of BKK members are employed in manufacturing-related occupations, as company health insurance funds are traditionally found primarily in companies in the manufacturing or processing industries. The regional distribution of employed BKK members largely corresponds to that of all employees subject to social insurance contributions in Germany; they are more commonly found in economically strong federal states such as Bavaria [29].

Routine data will be examined of persons who were continuously insured with one of the SHIs participating in the LCovB project from 01.01.2021 to 31.12.2023 (Module 1b: 01.01.2021 to 31.12.2024). In addition, the insured persons must be at least 18 years old at the beginning of the quarter in which the initial diagnosis (outpatient or inpatient) was documented. The two Modules follow different research objectives. Module 1a aims to examine the prevalence of PCS in relation to other diagnoses. Therefore, in the first data delivery for Module 1a, all insured individuals with ICD codes U07.1, U07.2, U08.9, U09.9!, and U10.9 are included. Module 1b focuses on the care trajectories of patients with PCS. Therefore, in the second data delivery for Module 1b, the diagnosis U09.9! serves as the inclusion criterion.

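### The one fully named Module 1 model takes incapacity for work yes/no as its outcome, which does not match the research question on long-term work disability and need for care

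*Protocol article*

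**What the plan says.** The further research questions of the protocol article include: "Which conditions lead to particularly long-term work disability and/or need for care in PCS patients". The Introduction sets the same priority: "It is also important to focus analyses on patients with particularly long periods of work disability and/or who are classified as eligible for a defined" (the sentence continues with the grade of care need). It also cites initial studies in which sick leave attributed to post-COVID was fairly rare in absolute terms but lasted more than 100 days on average.

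Under Data analysis, Module 1, the modelling of influencing factors is described in one sentence: "Binary logistic regressions (dichotomous dependent variable: incapacity for work yes/no) will be used to calculate the strength of various factors influencing the outcome". The same paragraph also plans descriptive statistics and stratified group comparisons of severity, progression and consequences, with incapacity for work as the example. It adds: "The relationship between specific constellations of care pathways and symptom severity will be investigated using bivariate and multivariate methods". It states the general emphasis as: "The focus of all analyses is the PCS diagnosis in combination with other diagnoses, healthcare measures received, and periods of incapacity for work".

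Table 1 lists, for both data deliveries, "Basic demographic data (year of birth, sex, municipality key, employment status, care level") and periods of incapacity to work. For Module 1b it adds long-term care claims. The Module 1 entry criteria concern insurance period, codes and age (adults, 18 or over when the quarter of first diagnosis starts). They contain no employment criterion and no upper age limit.

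**The concern.** The question concerns how long work disability lasts and whether patients come to need care. The stated outcome records only whether any incapacity occurred. Two things are lost. Short and long absences are pooled, so a factor that prolongs absence without making it more likely to start will look unimportant, and a factor that only adds short absences will look important. Care need does not enter the outcome at all, although it is the more relevant endpoint for the old and very old patients whom the article singles out.

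The results feed the expert panel's care recommendations. Odds ratios for any sick note could be presented there as if they identified what drives long-term disability.

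**Working it through.** There is no figure in the plan to reproduce: Module 1 has no sample size calculation, and the article gives no expected effect for this model. The check is a comparison of texts, followed by an illustration on assumed inputs.

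**1. Question against analysis**

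| Element of the question | Data collected (Table 1) | Outcome named in the Module 1 analysis |
|---|---|---|
| Long duration of work disability | Periods of incapacity | Incapacity yes/no; no duration or threshold |
| Need for care | Care level; long-term care claims (1b) | None |

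The other analyses in that paragraph do not fill the gap. The group comparisons name incapacity for work as a consequence without reference to its length. The unnamed multivariate methods relate care pathways to symptom severity. Periods of incapacity are called a focus, but no outcome is built from them.

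**2. What pooling short and long absences can hide**

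Assumed inputs, none of them from the article: risk of any incapacity p, the same in both groups; share of those cases that are long, q1 and q0.

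- Yes/no odds ratio = [p/(1−p)] / [p/(1−p)] = 1.0 for any p.
- Long-incapacity odds ratio = [p·q1/(1−p·q1)] / [p·q0/(1−p·q0)].

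With p = 0.50 and q0 = 0.10, the reference odds are 0.05/0.95 = 0.0526.

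- q1 = 0.20: 0.10/0.90 = 0.1111, and 0.1111/0.0526 = 2.11.
- q1 = 0.30: 0.15/0.85 = 0.1765, and 0.1765/0.0526 = 3.35.

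The result depends little on p. At p = 0.30 the two values are (0.06/0.94)/(0.03/0.97) = 2.06 and (0.09/0.91)/(0.03/0.97) = 3.20. At p = 0.70 they are (0.14/0.86)/(0.07/0.93) = 2.16 and (0.21/0.79)/(0.07/0.93) = 3.53.

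**3. Why the analysis population should be stated**

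The article does not say who enters the model. Suppose, as a condition and not as a reading of the plan, that adults without employment entered as 'no' and employment status was not adjusted for. Take a factor with no effect among the employed, whose carriers are employed in share s1 and non-carriers in share s0:

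- Odds ratio = [p·s1/(1−p·s1)] / [p·s0/(1−p·s0)].
- p = 0.50, s1 = 0.90, s0 = 0.50: (0.45/0.55)/(0.25/0.75) = 2.45.
- p = 0.50, s1 = 0.70, s0 = 0.50: (0.35/0.65)/(0.25/0.75) = 1.62.

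Restricted to the employed, both return to 1.0. Age is an obvious factor whose carriers differ in employment.

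**The case against.** The strongest defence is that a journal article condenses. The denominator, covariates and further models may stand in a full protocol or analysis plan that is not shown. The logistic model is also not the only Module 1 analysis: group comparisons of consequences are planned, and periods of incapacity, which carry duration, are named as a focus. The question is listed among the further ones; the two main questions, on the proportion with the diagnosis and on typical trajectories, do not depend on this model.

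Much of this stands. It lowers the severity and rules out saying that the question must go wholly unanswered. It does not remove the mismatch, because the article is not silent on the outcome: it states one, and that outcome differs from what the question asks. If yes/no was meant as long-term incapacity yes/no, the text does not say so.

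A reader might go further and infer that retirees and family-insured persons are counted as 'no', since the article reports: "Half of the BKK insured individuals (49,6%) are employed; 22.7% are family members; 19.8% are retired". The documents do not support that. No analysis population or coding is given for the regression, the entry criteria define the dataset and not each model's denominator, and employment status is available for restriction or adjustment. Nor can those shares be read as the part of the cohort not at risk of incapacity. They describe insured persons of all ages, including children among family members, whereas Module 1 takes adults with the relevant codes.

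**Conclusion.** The concern holds as a mismatch between the stated outcome and a stated secondary question. Followed as written, the regression describes who has any incapacity. It cannot separate long from short absence, and it does not address care need.

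The size depends on inputs that the article does not give. Under the assumptions shown (equal 50% risk of any incapacity, 10% versus 20% to 30% of cases long), a true odds ratio of 2.1 to 3.4 for long incapacity appears as 1.0. These figures show what the outcome can miss; they do not predict this study's results.

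The population at risk is a point to clarify. Confounding of age and other factors with employment would arise only if non-employed adults entered as 'no' without adjustment, which the article does not say. Severity is moderate.

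**What to change.** - Replace the yes/no outcome with cumulative incapacity days, or with a long-term threshold set in advance, counted in a fixed window after the first U09.9! code.
- State that this model is fitted in persons employed at the index quarter.
- Add a second model, with new or higher care level as the outcome, for the need-for-care part of the question.

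No new data are needed: incapacity periods, employment status and care level are in Table 1 for both deliveries, and long-term care claims are in Module 1b. The cost is a few sentences in the analysis section, modest programming and a smaller sample for the incapacity model. The window must also fit the data period, which ends on 31.12.2024 for Module 1b, so patients first coded late will lack full follow-up and need a stated rule. Results are not expected before November 2026. The definitions should be fixed before the outcome data are analysed.

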#### Module 2 (survey).

To analyse the standardized survey, descriptive statistics will be used to provide an overview of the data, and bivariate and multivariate methods (e.g., correlations, regressions) will be used to identify associations. Group comparisons regarding symptom severity, quality of life or health status will be stratified by gender, age or treatment history.

#### Module 3 (interviews).

The qualitative interviews will be analysed using Kuckartz's qualitative content analysis [44] and the MAXQDA software. This combines deductive, theory-driven perspectives with inductive, material-based approaches, thus enabling a differentiated view of the complex reality of healthcare for people affected by PCS.

#### Module 4 (medical visits and assessments).

A descriptive presentation of the physical examination (severity of the disease) and questionnaire surveys will be carried out by the visiting medical staff and a therapy concept initiated.

### Integration of the study findings

After each Module has been analyzed separately according to its own methodological standards, the results are compared and combined to expand our understanding by the convergent design [45,46]. By comparing multiple data types, the strengths of different methods are utilised. The respective results are combined to provide a more comprehensive and meaningful overall picture. The data from the qualitative part is intended to provide contextual information, in-depth insights and individual perspectives of the patients, whilst the data from the quantitative part of the study is intended to reveal prevalence estimates and care pathways. The analysis will examine which information in the data sources is consistent, complementary or contradictory, and this will be discussed and approved by the expert panel. The results are to be linked and presented by joint displays to integrate quantitative and qualitative data [47].

